#### Sex as a biological variable

We will examine the primary hypothesis and the two secondary hypotheses (see below) with respect to difference by sex. In particular, the primary analysis method will be used and a sex by treatment interaction in the time-averaged odds of viral suppression will be added to the model to test whether there are differential treatment effects by sex. With the expected 80 or 1/3 of the sample being women, there is reasonable power to uncover a difference.

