### Sample size {14}

Assuming *α* = 0.05, power=.80, and *N*=240, we computed the minimum detectable odds ratio (*OR*) and absolute proportion difference (*pdiff*), assuming the three post-intervention time points are part of the contrast. We varied the within-subject correlation *ρ* from 0.10 to 0.80. Power for a binomial is lowest when the base-rate (control group) probability (*P*_0_) is near 50%. Minimum detectable effects are 15% absolute difference in proportions and depend on the base-rate of suppression in the standard of care (*P*_0_) and the level of autocorrelation. This size of effect falls within published cutoffs of small to medium effect sizes [39].

Power analyses were generated using the generalized estimating equations-based two-group repeated proportion module in NCSS PASS 2020 to compute minimum detectable effect sizes for the proposed primary analysis. The study will begin with 240 participants evenly assigned to the intervention and control groups (80 per city). Our primary analysis strategy will assume any participant dropping out of the study has not achieved the outcome.

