#### Primary inferential analyses to address primary aim (Hypothesis 1)

We hypothesize that, for those randomized to the *THR* arm, the odds of our primary outcome, HIV viral suppression, will be higher than for those randomized to off-site linkage to HIV care (control) arm (Hypothesis 1). Generalized estimating equations (GEE) [54] will be used to perform the proposed primary analysis, which is a planned time-averaged comparison of post baseline measurements of HIV viral suppression across the *THR* and control groups to test primary Hypothesis 1. Alpha will be set at 0.05 for this planned comparison. Planned post hoc comparisons will examine the difference between conditions at each of the three assessment times.

Though GEE estimates are consistent even if the correlation structure is mis-specified, GEE’s statistical efficiency improves as the working correlation structure more closely approximates the actual correlation structure, so various correlation structures suitable for the study’s design will be considered (e.g., exchangeable, autocorrelated, *m*-dependent, unstructured). The QIC statistic will be used to select the final correlation structure. Recruitment city (Miami vs. Tampa or Ft. Lauderdale) will be included in all models as required by the stratified randomized design to obtain unbiased results. Robust standard errors will be used to obtain correct inferences even if the chosen correlation structure remains slightly mis-specified. All analyses will include outlier and influential case screening via computation of GEE-based residual analysis, including leverage, DFBeta, and Cook’s D statistics. If outliers are found, results will be reported with and without outliers included.

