#### Sex as a biological variable

We will examine each of secondary hypotheses (2a, 2b, 3a, and 3b) with respect to difference by sex. In particular, the respective analysis method will be used and a sex by treatment interaction to test whether there are differential treatment effects by sex.

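### The claim of reasonable power for the sex-by-treatment interaction is unsupported: near 50% suppression, an interaction as large as the planned 15-point effect has only about 22–41% power

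*Protocol article*

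**What the plan says.** The first section headed Sex as a biological variable, which follows the primary analysis, adds a sex-by-treatment term to the GEE model for time-averaged viral suppression, on the odds scale. It then states: "With the expected 80 or 1/3 of the sample being women, there is reasonable power to uncover a difference". It gives no effect size, power figure or calculation.

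The only power calculation is in Sample size {14}, and it covers the overall two-arm contrast. There, "The study will begin with 240 participants evenly assigned to the intervention and control groups (80 per city"), power is set at 0.80, and "Minimum detectable effects are 15% absolute difference in proportions". The calculation was made "assuming the three post-intervention time points are part of the contrast", with the within-subject correlation varied "from 0.10 to 0.80". No control rate is fixed. The section says only that "Power for a binomial is lowest when the base-rate (control group) probability" is near 50%. For the primary comparison, "Alpha will be set at 0.05 for this planned comparison".

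Sequence generation {16a} allocates 1:1 and stratifies by site and by gender (also called biological sex). The second section headed Sex as a biological variable extends the approach to hypotheses 2a, 2b, 3a and 3b through "a sex by treatment interaction to test whether there are differential treatment effects by sex", and makes no statement about power.

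**The concern.** The sample size was worked out for a comparison of 120 with 120 participants. The interaction is a difference between two such comparisons, each made in part of the sample, and the smaller part has only 80 people. It is estimated much less precisely than the overall effect, so a sample that just suffices for the overall effect cannot also give good power for an interaction of similar size.

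What is at stake is how the sex analysis will be read. If the protocol declares the test adequately powered, a non-significant result could encourage the conclusion that the intervention works about equally in women and men. In fact the test would more often than not miss a 15-point benefit confined to one sex when suppression is near 50%.

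**Working it through.** **Inputs from the protocol article.** N = 240, 120 per arm; power 0.80; alpha 0.05; three follow-up measurements; correlation ρ from 0.10 to 0.80; detectable overall difference 15 points (Sample size {14} and the primary analysis section). 80 women, hence 160 men (Sex as a biological variable). Allocation 1:1 within sex strata, hence about 40 vs 40 women and 80 vs 80 men (Sequence generation {16a}). Dropouts count as not suppressed, so N stays at 240.

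**Assumptions added here.** Two-sided test; exchangeable correlation; suppression near 50%, so that p(1 − p) ≈ 0.25 in every cell.

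**Step 1: reproduce the plan's own figure.** Averaging three correlated measurements multiplies the variance by f = (1 + 2ρ)/3. The overall standard error is √(2 × 0.25 × f/120), and the detectable difference is 2.802 times that (1.960 + 0.842). This gives 11.4 points at ρ = 0.10, 14.8 at 0.50 and 16.8 at 0.80. As a cross-check, 50% vs 65% at a single time point needs 170 per arm; 170 × (1 + 2 × 0.55)/3 = 119 per arm, or 238 in total against the planned 240. The stated 15 points is therefore reproduced at ρ of about 0.50 to 0.55, inside the stated range.

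**Step 2: interaction against main effect.** With equal cell variances, the ratio of standard errors is √[(1/40 + 1/80)/(1/120)] = √4.5 = 2.12. If the overall test has exactly 80% power, an interaction of the same size has power Φ(2.802/2.12 − 1.96) = Φ(−0.64) ≈ 26%. Equal power would need 4.5 times the sample.

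**Step 3: power and detectable interaction.** SE(int) = √[2 × 0.25 × f/40 + 2 × 0.25 × f/80]. Power for 15 points is Φ(0.15/SE − 1.96). The detectable interaction at 80% power is 2.802 × SE. Near 50%, the matching ratio of odds ratios is about exp(4 × detectable difference).

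| ρ | f | SE(int) | Power for 15 points | Detectable at 80% power | Ratio of odds ratios |
|---|---|---|---|---|---|
| 0.10 | 0.400 | 0.0866 | 41% | 24 points | 2.6 |
| 0.50 | 0.667 | 0.1118 | 27% | 31 points | 3.5 |
| 0.80 | 0.867 | 0.1275 | 22% | 36 points | 4.2 |

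A 15-point interaction means, for example, the whole planned effect in one sex and none in the other.

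**Step 4: sensitivity.** The control rate was varied from 20% to 50%, along with the way a 15-point gap is divided between the sexes. On the odds scale, which the plan uses, power runs from about 20% to 47%. On the difference scale the highest value is about 55%, at a control rate of 20% and ρ = 0.10. No variant reaches 80%.

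**Step 5: two reference points.** A 15-point effect tested in the 80 women alone (42.5% vs 57.5%) has standard error √[2 × 0.2444 × f/40], and so power of 57% at ρ = 0.10 and 31% at ρ = 0.80. An interaction of 30 points (no effect in women, 30 points in men) has about 61% to 97% power on the odds scale, depending on the control rate and ρ.

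**The case against.** The strongest reply is that the sentence contains no figure, so no figure in it is miscalculated. The plan never says which interaction it hopes to detect; the 15-point benchmark is taken from the overall comparison, and an interaction of 30 points would have fair to high power. That stands as a description: this is an unsupported claim, optimistic for any interaction up to the size of the planned effect, and not a slip of arithmetic. It does not rescue the sentence, because nothing in the document suggests that so large a difference between the sexes is expected.

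Several stronger readings are tempting and should be resisted:

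- A reader might infer that the plan will treat a null interaction as proof of equal effects. Neither section on sex says how a non-significant result will be interpreted.
- A reader might take the factor 2.12 as holding for any base rate. The correlation factor cancels if it is common to all cells, but the base rate does not unless the cell variances are similar. With suppression of 20% in women and 50% in men, the ratio to a sex-stratified main effect is √(0.01425/0.003667) = 1.97; with the rates reversed it is √(0.0165/0.003167) = 2.28. The conclusion is unchanged.
- A reader might take 22–41% as unconditional. It depends on suppression near 50%, which the plan names only as the least favourable case. Counting dropouts as failures could push observed rates lower, which is why the wider ranges in the working belong beside it.
- A reader might count the secondary-hypothesis section as a second instance of the error. It repeats the test but claims no power, and the plan gives no base rate or target effect for those outcomes, so the 15-point benchmark does not carry over.

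It is also fair that this is a secondary analysis of effect modification, and that fuller reporting rules can be left to the analysis plan. An unseen analysis plan does not excuse a positive claim that the protocol itself makes.

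**Conclusion.** The concern holds, for the one sentence in the primary-analysis section on sex. The design does not have reasonable power for a sex-by-treatment interaction up to the size of the planned overall effect. The added assumptions (a two-sided test, exchangeable correlation, suppression near 50%, and women and men split evenly between arms) all bear on the central 22–41% figure, but the finding that power falls well short of 80% survives every control rate, scale and split between the sexes that was tried. Only an interaction around twice the planned effect would make the statement true, and the plan names none. The primary comparison, its sample size and its alpha are not affected.

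**What to change.** In the first section headed Sex as a biological variable, replace the power sentence with the detectable interaction and its assumptions. For example: with about 80 women and 160 men, a two-sided 5% test, within-subject correlation of 0.10 to 0.80 and suppression near 50%, the interaction detectable with 80% power is about 24 to 36 percentage points. Label the sex-by-treatment tests exploratory, in both sections on sex. State that the interaction estimate will be reported with its 95% confidence interval, so that a non-significant result is not taken as evidence of equal effects.

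The cost is one replaced sentence and a short reporting statement. No participants, data or design changes are needed.

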#### Data analysis plan and statistical procedures to address secondary hypotheses

For preliminary analyses and missing data, the secondary analyses will use the same preliminary analysis and missing data strategy as Hypothesis 1. Hypothesis 2 is that *THR* will be superior to off-site linkage to HIV care in achieving (1) initiation of MOUD and (2) retention in MOUD as evidenced by positive UDS for MOUD. Hypothesis 3 is that *THR* will be superior to off-site referral and off-site linkage to HIV care in achieving (1) initiation of medication (DAA) for HCV Cure and (2) HCV cure as evidenced by undetectable HCV RNA at 12 weeks post HCV treatment (SVR12).

Hypotheses 2a and 3a will be tested using a logistic regression model where the dependent measure is equal to zero if the individual does not initiate the medication prior to the end of the study (month 12) and is equal to 1 if the individual does initiate the medication prior to the end of the study. We will test whether *THR* relative to the control group increases the odds of initiating the respective medication. Note that for Hypothesis 2a the sample is all participants, whereas, for 3a, it is only those eligible for HCV treatment, i.e., who have a positive HCV viral load at baseline.

Hypotheses 2b will be tested as will be Hypothesis 1, with GEE as a time-averaged comparison of post-initiation of MOUD measurements of presence of MOUD by UDS between those randomized to *THR* and the control condition. To maintain this hypothesis test as an intention to treat analyses, in the initial test, all participants will be included. Those who have not initiated will be coded as not retained. In a planned post hoc comparison, the sample will be reduced to only those who have initiated to examine whether there is a difference in rates of retention conditional on initiation.

Hypothesis 3b will be tested as will be H2a and H3a using logistic regression. Initial intent-to-treat analyses will compare the odds of achieving HCV cure in the 12 months post randomization within the *THR* arm relative to the control arm within the full sample that was HCV positive at baseline. Planned post hoc comparisons will repeat this analysis within the sample that initiated HCV treatment to examine whether there were significant differences conditional on initiation.

The alpha will be set at .05 for each these secondary hypotheses (2a, 2b, 3a, and 3b). In each model, recruitment site (Miami vs. Tampa or Ft. Lauderdale) will be included in these analyses as required by the stratified randomized design to obtain unbiased results. To maximize rigor, appropriate diagnostics including outlier and influential case screening will be examined for each model. If outliers are found, results will be reported with and without outliers included.

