### Objectives {7}

The primary objective is to compare the efficacy of *THR* for initiation of ART at SSPs vs. off-site linkage to an HIV clinic with respect to viral suppression across follow-up (suppression at 3, 6, and 12 months post randomization). Participants with HIV RNA<200 copies/ml will be considered virally suppressed.

The primary hypothesis is that *THR* will be superior to off-site linkage in achieving HIV RNA<200 copies/ml measured by the proportion of participants virally suppressed across follow-up (time-averaged viral suppression).

The secondary objectives are to measure differences between study arms in MOUD initiation and HCV cure. Participants in the *THR* arm will have enhanced access to medical and mental health clinician visits via a telehealth platform and remote phlebotomy in addition to medication management (e.g., storage in pill lockers at SSP, weekly delivery) and appointment reminders. Participants assigned to the off-site linkage arm will be linked to a traditional Ryan White clinic by SSP staff as is currently the standard of care. MOUD initiation is measured by buprenorphine, naltrexone, or methadone on urine drug screen (UDS). HCV cure (i.e., HCV RNA undetectable) is defined as sustained virologic response after completing direct acting antivirals (DAA), i.e., SVR12. Mediating effects of the intervention on injection risk behaviors (i.e., syringe reuse and syringe sharing) will also be assessed.

For the economic analysis, *THR* is expected to have a higher cost but be more effective in increasing uptake of ART, MOUD, and DAA, as well as HIV viral suppression, MOUD retention, and HCV cure among PWID participants. Incremental cost-effectiveness ratios (ICERs) will be calculated to report the additional cost per unit of desired outcome (e.g., increased ART and MOUD initiation) in the *THR* vs. off-site linkage to HIV care arms.

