### Eligibility criteria {10}

Eligibility criteria include the following: (1) age 18 or older; (2) able to speak English; (3) enrolled in IDEA Miami, IDEA Tampa, or the SPOT SSPs; (4) injection drug use in past 12 months by self-report; (5) willing and able to sign informed consent, provide locator information and medical records release; (6) testing reactive for HIV by rapid test; and (7) HIV RNA>200 copies/ml as determined by on-site labs or abstracted medical records (result within 3 months of randomization date). Of note, pregnant people are eligible for enrollment in this trial.

Exclusion criteria include the following: (1) testing HIV negative via rapid test; (2) receipt of THR intervention in the past 6 months; (3) inability to provide informed consent; (4) planning to leave the area within 12 months; (5) principal or site investigator discretion; (6) currently in prison or jail; and (7) enrollment in NIDA Clinical Trials Network CTN 121. Investigator discretion could include serious medical, psychiatric, or co-occurring substance use disorder that acutely requires a higher or different level of care including the following: (1) disabling or terminal medical illness (e.g., decompensated heart failure, cirrhosis, or end-stage liver disease); (2) severe, untreated, or inadequately treated psychiatric condition (e.g., active psychosis); (3) in need of medical detox for severe alcohol, benzodiazepine, or other depressant or sedative hypnotic use; (4) suicidal intent or plan; or (5) homicidal ideation.

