If participants have co-occurring mental health disorders, peers can use telehealth to connect the participants to the SSP’s on-site psychologist for mental health treatment. The psychologist will consult with the study clinician about any mental health diagnoses so that appropriate prescriptions can be initiated (e.g., SSRI for depression or anxiety). *THR* medical services include management of HIV, SUD, and other comorbidities. Infections such as skin and soft tissue infections will be treated with antibiotics, and any required procedural intervention will be referred to on-site wound care at the SSP. Physician visits are available to patients on-demand during most business hours and coordinated by the study team. All participants with OUD are repeatedly offered initiation of buprenorphine-naloxone or naltrexone, navigation to methadone programs, and naloxone for overdose prevention. Participants with chronic HCV infection are offered treatment with DAAs. Participants are screened for sexually transmitted infections and navigated to treatment when necessary. THR medical care will take an adaptive approach based on patient vulnerability (e.g., unstable housing, severe SUD, concurrent SUDs) as outlined in the THR Intervention Manual. The adaptive approach will, at the discretion of the study clinician, appropriately address patient needs (e.g., medications for stimulant use, medications for alcohol use disorder). If residential treatment for SUD is requested and appropriate, the peer will work with the participant and SSP staff to link to Ryan White or other treatment beds. This multidisciplinary team will assist the patient for 12 months, bringing the technology (i.e., traveling with iPad and WiFi hotspot) and *THR* to the participant where they are located. After the study period, the study participant will be offered continuation in the *THR* program.

Participants in the *THR* arm will have all intervention sessions audio recorded (i.e., physician, psychologist and peer encounters). Participants will be given the option to opt out of being audio-recorded.

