### Outcomes {12}

Table 1 shows the outcomes.

**Table 1 Tab1:** Outcomes

Primary outcomes	Definition	Measure
Viral suppression	HIV viral load <200 copies/ml	HIV viral load <200 copies/ml time-averaged over 3, 6, and 12 months post baseline
Secondary outcomes	Definition	Measure
Initiation of MOUD	Receiving prescription and taking first dose of buprenorphine, naltrexone, or methadone	Positive UDS for buprenorphine, naltrexone, or methadone at study follow-up visit after MOUD is prescribed
HCV cure	Achieving 12-week sustained virologic response	HCV treatment initiated resulting in negative HCV RNA at 12 weeks post treatment completion
Cost-effectiveness	Cost per unit of a desired outcome (e.g., cost per viral suppression; cost per HCV cure)	Incremental cost-effectiveness ratios (ICERs) over 3, 6, and 12 months post baseline.

The primary trial outcome is HIV viral suppression. Viral suppression will be defined as HIV RNA <200 copies/ml which will be time-averaged HIV viral suppression over 3-, 6-, and 12-month follow-up. Secondary outcomes include initiation of MOUD defined as receiving a prescription and taking first dose of buprenorphine, naltrexone, or methadone. MOUD initiation will be measured by UDS positive for buprenorphine, naltrexone, or methadone at study follow-up visit at 3, 6, or 12 months. An additional secondary outcome is HCV cure, defined as achieving 12-week sustained virologic response. HCV cure will be measured by negative HCV RNA at 12 weeks post treatment completion.

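### Hypothesis 2a tests MOUD initiation in all participants, with or without OUD and including any already on MOUD, and the definition and measure of initiation disagree for those already on it

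*Protocol article*

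**What the plan says.** All references are to the protocol article.

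- **Analysis sample** (section on the secondary hypotheses): "Note that for Hypothesis 2a the sample is all participants, whereas, for 3a, it is only those eligible for HCV treatment". The same sentence identifies the HCV group by a positive viral load at baseline. The logistic outcome for 2a "is equal to 1 if the individual does initiate the medication prior to the end of the study". Hypothesis 2b, retention on MOUD, also takes everyone in its initial test and codes those who have not initiated as not retained.
- **Entry** (Eligibility criteria): "injection drug use in past 12 months by self-report". No listed inclusion criterion requires OUD, and no listed exclusion covers current MOUD.
- **Who is offered MOUD** (Tele-Harm Reduction intervention arm): "All participants with OUD are repeatedly offered initiation of buprenorphine-naloxone or naltrexone". In the control arm, MOUD comes through the off-site clinic.
- **Definition of initiation** (Table 1 under Outcomes): "Receiving prescription and taking first dose of buprenorphine, naltrexone, or methadone".
- **Measure of initiation** (Table 1): "Positive UDS for buprenorphine, naltrexone, or methadone at study follow-up visit after MOUD is prescribed". The text below the table is looser: "MOUD initiation will be measured by UDS positive for buprenorphine, naltrexone, or methadone at study follow-up visit at 3, 6, or 12 months". The Objectives section likewise relies on the drug being found on UDS, with no condition on baseline status.

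**The concern.** Two groups in the 2a sample cannot show a treatment effect on initiation. Participants without OUD have no stated route to MOUD in the intervention arm and would score 0 in either arm. Participants already on MOUD at entry cannot newly start it. If they stay on it, their follow-up UDS is positive and the measure scores them 1, although nothing was initiated during the trial. The plan handles the parallel HCV question by limiting 3a to those treatable at baseline, but it does not do so for MOUD.

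At stake are the size of the estimated effect, the power of a test with its own 0.05 level, and the meaning of the outcome. A weak result could not separate an ineffective intervention from a sample in which many could not respond. MOUD initiation is also an example of an outcome unit for the cost-effectiveness ratio in the Objectives, so the same ambiguity carries into that ratio.

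For 2b, which uses measurements after initiation, a participant already on MOUD has no on-study starting point.

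**Working it through.** **Plan's own figure.** The plan states no rate, effect size or power for 2a. The 15-point minimum detectable difference under Sample size concerns viral suppression only and has no part in this check.

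**Inputs from the document.** 240 participants, 1:1, so 120 per arm; alpha 0.05 (taken as two-sided, since sidedness is not stated).

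**Assumed inputs.** Initiation of 30% (control) vs 50% (THR) among those able to initiate; a share *f* without OUD, who never start; a share *g* already on MOUD at entry, who stay on it.

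**Formulas.** Share able to initiate: e = 1 − f − g. Observed arm rate: e·p + c·g, with c = 1 if existing users count as initiators and c = 0 if they do not. The risk difference is therefore e × 20 points whatever c is.

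Power = Φ[(d − 1.96·s0)/s1], with s0 = √(2·p̄(1−p̄)/n) and s1 = √((p0(1−p0) + p1(1−p1))/n). For the restricted set the rates are 30% vs 50% and n = 120e per arm.

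**First case in full (f = 0.25, g = 0).**
- All participants: 0.75 × 0.30 = 0.225 and 0.75 × 0.50 = 0.375, so d = 0.15. s0 = 0.0592, s1 = 0.0584; (0.15 − 0.1160)/0.0584 = 0.583; power 0.720.
- Restricted, 90 per arm: s0 = 0.0730, s1 = 0.0715; (0.20 − 0.1431)/0.0715 = 0.795; power 0.787.

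| f | g | Existing users coded | All participants | Difference | OR | Power, all | Power, restricted (n/arm) |
|---|---|---|---|---|---|---|---|
| 0.25 | 0 | n/a | 22.5% vs 37.5% | 15 points | 2.07 | 0.720 | 0.787 (90) |
| 0.15 | 0.10 | 1 | 32.5% vs 47.5% | 15 points | 1.88 | 0.662 | 0.787 (90) |
| 0.15 | 0.10 | 0 | 22.5% vs 37.5% | 15 points | 2.07 | 0.720 | 0.787 (90) |
| 0.30 | 0.10 | 1 | 28% vs 40% | 12 points | 1.71 | 0.501 | 0.691 (72) |
| 0.30 | 0.10 | 0 | 18% vs 30% | 12 points | 1.95 | 0.587 | 0.691 (72) |

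The true difference and OR among those able to initiate are 20 points and 2.33.

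**Participants without OUD alone (g = 0).** Power rises on restriction from 0.832 to 0.856 at f = 0.10, from 0.760 to 0.812 at f = 0.20, and from 0.720 to 0.787 at f = 0.25. With lower assumed rates of 10% vs 25% and f = 0.25, it rises only from 0.735 to 0.759.

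**Imperfect baseline ascertainment (first case).** If baseline data identify only 85% of those able to initiate, n = 0.85 × 90 = 76.5 per arm and restricted power is 0.718, against 0.720 unrestricted. At 80%, n = 72 and power is 0.691. Both still exceed the 0.662 of the second row, where existing users count as initiators.

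**Definition against measure.** Take a participant on MOUD at entry who remains on it. Under the outcome text and the Objectives, a positive follow-up UDS scores 1. Under the definition, if the first dose must fall within the trial, the score is 0. Table 1's condition that the UDS follow a prescription does not decide the matter, because this participant already holds one. The sources give different scores for the same person.

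**The case against.** The strongest defence is that comparing everyone randomised is a valid intention-to-treat test. The arms are balanced in expectation, and the result answers a coherent programme-level question: how many enrolled people who inject drugs end up on MOUD under each strategy. That stands. A reader might infer that the 2a test is biased or invalid; the document does not support this. The loss is in power, effect size and interpretation, on a secondary outcome for which no power is claimed.

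A reader might also infer that the plan definitely counts existing users as initiators. That goes too far. The Table 1 definition and its prescription condition allow a stricter reading, and the logistic outcome speaks of the individual initiating. The coding is unreconciled rather than settled, and the larger power losses in the table depend on the looser reading.

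Three further points stand. All shares and rates are assumed, and both groups may be small. OUD needs a diagnostic measure, whereas HCV eligibility is a single laboratory result, so the parallel with 3a is imperfect; restriction also drops anyone whose OUD is recognised only later. And the baseline data are not clearly documented: laboratory assessments occur at month 0, but a month-0 UDS is not stated, and the footnote to the assessment table names a CIDI and a drug and alcohol measure without saying that OUD is diagnosed.

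Intention to treat does not, however, require the all-participants sample. Restricting on status recorded before randomisation preserves the randomised comparison, and the plan itself describes 3b as intent-to-treat within those HCV-positive at baseline. The planned follow-up to 2b, limited to those who initiated, conditions on a post-randomisation event and is no substitute.

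**Conclusion.** The point holds as an avoidable weakness in 2a, and by extension 2b. The article fixes a sample that can include people who could not initiate, and gives a definition and a measure that disagree for anyone already on MOUD. Under the assumed 30% vs 50%, the observed difference falls from 20 points to 12–15. Power is about 0.07 to 0.10 below the restricted analysis if existing users are coded 0, and about 0.13 to 0.19 below it if they are coded as initiators, for the shares in the table. Mixing in participants without OUD alone costs little, 0.02 to 0.07. The direction of the dilution does not depend on the assumed shares, provided that some such participants enrol and those without OUD do not start MOUD; its size does. Reconciling definition and measure is worthwhile whatever the shares turn out to be.

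**What to change.** 1. Reconcile the definition and the measure so that 2a counts only MOUD newly started after randomisation, and state how participants already on MOUD at entry are coded.
2. Test 2a in participants with OUD and not on MOUD at baseline, using status recorded before randomisation, in parallel with 3a. Test 2b in those with baseline OUD.
3. Keep the all-participants analyses as supportive.
4. Confirm that the baseline instruments identify OUD and that current MOUD is recorded at month 0, by UDS, records or self-report.

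The cost is mainly wording, and the article says the analysis plan is finalised before data lock, so there is still room for it. If item 4 fails, baseline data collection would need adding, and participants already enrolled may lack it. The downside is a smaller analysis set. In the case with 25% without OUD, the power gain disappears if baseline ascertainment misses about 15% or more of those who could initiate.
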